#### **COVID-19 additional surveys**

Patients whose treatments are delayed, may still complete the 1, 2, 3, and 4 month follow up surveys without being seen for their laser treatments. When the non-essential visits open back up, patients will complete the rest of their treatments and complete the corresponding visit surveys. Since these are additional surveys that were not a part of the original consent, the patient will be asked to voluntarily sign an addendum demonstrating their willingness to complete the surveys. These additional surveys will replicate the corresponding visit surveys previously mentioned. To assist with the costs and time spent participating in the study, a \$20 research debit card will be given to the patient or their legal guardian at the end of the visit or mailed to the legal guardian's address (or patient's address if 18 years of age or older) upon successful completion of the surveys.

6.5 If there are plans for long-term follow-up (once all research related procedures are complete), what data will be collected during this period.  
N/A

6.6 For Humanitarian Use Device (HUD) uses provide a description of the device, a summary of how you propose to use the device, including a description of any screening procedures, the HUD procedure, and any patient follow-up visits, tests or procedures. N/A

## **7.0 Data and Specimen Banking\***

7.1 All demographic, clinical, and outcome data will be recorded by trained study staff in the REDCap database maintained at Nationwide Children's Hospital. REDCap is a network software suite that provides data storage, encryption, and password protection for health information, to which only study staff will have access. Privacy and security will be maintained by minimizing the amount of identifiable data collected. Local

data will be stored on computers located within The Center for Surgical Outcomes Research ([name]) facilities that are maintained on secure networks. All data and records generated during this study will remain confidential. All documents will be used solely for this study. De-identified data will be stored indefinitely as part of a repository.

7.2 MRN, Name, Phone Number, MyChart User or Not, Home Address, Email ID, Age, Race, Ethnicity, Gender, Insurance Coverage Status, Socioeconomic Data, Medications, Labs, Medical History Related to Pilonidal Disease, Family History of Pilonidal Disease, Current Pilonidal Disease Symptoms, Physician Office Visit, Emergency/Urgent Care Visit, Inpatient Visits for Pilonidal Disease

7.3 Privacy and security will be maintained by minimizing the amount of identifiable data as much as possible. Only study identifications (IDs) will be used to identify patients on all data forms and all datasets used for analysis. The file linking study IDs to patient names and medical record numbers (MRNs) will be password protected and will not be made available to non-study staff or used during data analysis. All study information will be compiled in REDCAP, to which only study staff will have access. There are no plans at this time to use the data collected in this study for a future research. In the event that a comparative study is planned in the future we will apply for approval to retrospectively review all procedures used for the treatment of pilonidal disease, which would include the patient population from this study amongst others.

## **8.0 Sharing of Results with Subjects\***

8.1 The final study results will not be shared with participants individually. However, at some time, a final study summary will be available on the ClinicalTrials.Gov (<http://clinicaltrials.gov>) website.

## **9.0 Study Timelines\***

9.1 *Describe:*

- The duration of an individual subject's participation in the study is two years.
- Anticipated enrollment will be completed 09/01/2021.
- Estimated completion of final submission to grant is 8/15/2023.

## **10.0 Inclusion and Exclusion Criteria\***

10.1 All potentially eligible patients treated for pilonidal disease at NCH, OSU, or one of the community pediatric practices will be informed of the study. If they do want more details, they will ask for permission to provide their contact information to the study team. Subsequently, a trained member of the research team will contact the patient and family to assess their eligibility against both inclusion and exclusion criteria. If all

eligibility criteria are met, the patient and legal guardian (if < 18 years of age) will be invited to enroll. At the initial clinic visit, a trained member of the research team will confirm the patient is eligible.

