## **4.0 Study Endpoints**

4.1 The primary outcome is the rate of recurrent pilonidal disease at 1 year defined as development of a new pilonidal abscess, folliculitis, or draining sinus after treatment, which would require antibiotic treatment, additional surgical incision and drainage, or excision within 1 year of enrollment.

Secondary outcome include: differences in disability days of the patient at 1 year, disability days of the caregiver at 1 year, HRQOL, health care satisfaction, disease-related attitudes and perceived stigma, rates of

PROTOCOL TITLE: A randomized controlled trial of laser hair depilation in adolescents with pilonidal disease

pilonidal disease-related complications, rates of pilonidal disease related procedures (incision and drainage), surgical excision, and post-operative complications, and rates of compliance with recommended treatment.

A summary of the outcomes that will be assessed are listed in the table below (Table 2).

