#### Exclusion Criteria

- History of photosensitivity
- Actively inflamed pilonidal sinus. These patients will be informed of the trial and invited to contact the study team upon resolution of their inflamed sinus if they are interested in being in the trial at that time.

10.3 Our study will include children and teenagers. It will exclude adults unable to consent, pregnant women, and prisoners.

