### 12.0 Local Number of Subjects

12.1 The sample size needed to assess the primary outcome of the proportion of patients with recurrent pilonidal disease at 1-year is based on: 1) previous published studies and institutional data on the recurrence rates of pilonidal disease and 2) the efficacy of laser hair depilation treatment to reduce pilonidal disease recurrence in previous studies and our institutional pilot study. In this RCT, the recurrence rate within 1 year is expected to be 12% in the control group and a maximum 2% in the laser group. Based on these estimated recurrence rates, under a group sequential design with one interim and one final analysis, an overall type I error rate (two- sided) of 5 % and power of 80%, the sample size required for this trial is 122 patients in each treatment group. Assuming a 10% drop out rate over the course of the 1 year follow-up, we will plan to enroll 136 patients in each group (total; n=272 patients).

The gap in the laser treatments caused by COVID-19 created a gap in when we could begin laser treatments in newly enrolled patients by 1-3 months. Since a laser patient's participation in the study begins at their first laser treatment, no data has been collected on these patients. Patients in the group have reported no longer being interested/able to receive

treatments due to concerns about COVID and visits to the hospital to receive laser treatments. This group of about 15 patients was not anticipated for our sample size calculation but are needed for the primary outcomes data. In order to maintain the required power in our analyses, our statistician recommends enrolling and randomizing an additional 30 patients, thereby increasing our sample size to 302 patients (151 in each group).

12.2 If applicable, distinguish between the number of subjects who are expected to be enrolled and screened, and the number of subjects needed to complete the research procedures (i.e., numbers of subjects excluding screen failures.) -N/A

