### 13.0 Recruitment Methods

13.1 All potentially eligible patients treated for pilonidal disease at NCH, OSU, or one of the community pediatric practices will be informed of the study. All potential patient recruitment sites will have flyers and pamphlets advertising the study. Study team members will contact sites monthly to answer questions and provide additional information and study related materials as needed. Clinic schedules will be reviewed by members of the research team and providers seeing patients with pilonidal disease will be asked if they can be approached about the study. Nurses in each of the clinics will be informed of the study and inform patients about the study and provide study contact information to the patient and their family. In addition, they will ask the patient and family if they would like additional information on the study. If they do want more details, they will ask for permission to provide their contact information to the study team. Subsequently, a trained member of the research team will contact the patient and family to assess their eligibility against both inclusion and exclusion criteria. If all eligibility criteria are met, the patient and legal guardian (if < 18 years of age) will be invited to enroll. The research team member will review the information about the study and answer any questions. If they remain interested in enrolling, they will be scheduled for a clinic visit. At the initial clinic visit, a trained member of the research team will review the study protocol and procedures and the risk and benefits of each treatment with the patient and caregiver again, answer any additional questions, and written informed consent and assent (for patients < 18 years of age) will then be obtained.

If a patient is enrolled into the study at a telehealth visit, a trained member of the research team will contact the family to obtain phone or electronic-consent. At the end of the telehealth video visit, if the patient verbally states they are interested in the study, a trained member of the study will join the telehealth call through EPIC by invite of the principal investigator. The trained member will review the study protocol and procedures and the risk and benefits of each treatment with the patient and caregiver, answer any questions, and phone/ electronic-consent and assent (for patients < 18

PROTOCOL TITLE: A randomized controlled trial of laser hair depilation in adolescents with pilonidal disease

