**Figure 2: Conceptual Model**

[figure not shown]

17.2 Patients that consent to enroll will be randomized using a randomized block scheme, with blocks of varying size. The sequence will be built using the plan procedure in SAS 9.4 (SAS Institute Inc., Cary, NC). It will be generated and maintained by the project statistician and will be unavailable to other research study members. Blocks will be of size four or six, with the lengths chosen randomly with equal probability. This block design assures a balanced allocation to the two treatment groups, both at the end of trial enrollment and at periodic intervals throughout enrollment. The varying block size also reduces the chance that research personnel will be able to guess the next intervention group assignment and, thus, minimizes any unconscious bias in patient allocation. Stratification will not be incorporated into the randomization scheme because, based on the current literature, there are no patient characteristics, including the number of previous episodes of disease, the types of previous treatments, or disease severity, that are consistently strongly associated with the probability of recurrence. Furthermore, all subgroups defined by these characteristics are expected to be large enough that the risk of imbalance in these characteristics is unlikely, though this will be monitored.

A web-based randomization and registration process will be designed to verify inclusion/exclusion criteria and then randomize eligible patients (using the earlier generated randomization list). These data will reside behind the Nationwide Children's Hospital (NCH) firewall for security. All data including the registration and randomization will be backed up incrementally daily with a full backup weekly. Tracking and error reports will be generated to alert study staff of any data quality issues as they arise. Research staff will follow up on any instances of incomplete or problem data. All baseline and outcome data will be stored electronically

1077 in a Research Electronic Data Capture (REDCap) database, which can be  
1078 accessed only by the appropriate research staff. Given the nature of the  
1079 intervention proposed, participants and research team members will know  
1080 the intervention to which they have been assigned.

1081 17.3 See sections 17.1 and 17.2

1082 17.4 Describe how data or specimens will be handled study-wide:

- 1083 • MRN, Name, Phone Number, MyChart User or Not, Home  

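### A patient who consents by telehealth can be allocated in this open trial before the clinic visit that confirms eligibility, and no analysis set keeps those lost after allocation in the 1-year comparison

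*Combined protocol and SAP*

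**What the plan says.** On the in-person route, section 13 obtains consent at the initial clinic visit. Section 10.1 confirms eligibility at the same visit: "At the initial clinic visit, a trained member of the research team will confirm the patient is eligible". The steps coincide.

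On the telehealth route (13.1, the paragraph beginning "If a patient is enrolled into the study at a telehealth visit"), consent is taken by phone or electronically at the end of a video visit. The section gives no time of randomisation and asks for no in-person visit first. Section 17.2 says "Patients that consent to enroll will be randomized using a randomized block scheme, with blocks of varying size". It adds that the web system checks the entry criteria before it randomises, and that participants and the research team will know the assignment.

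One of the two listed exclusions can change over time: "Actively inflamed pilonidal sinus". Affected patients are invited back after resolution.

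Section 12.1 reports that the pandemic delayed the ability to "begin laser treatments in newly enrolled patients by 1-3 months". It places the start of a laser patient's participation at the first laser treatment, says no data were collected on these patients, and raises the total from 272 to 302 to replace about 15 of them. Section 4.1 counts recurrence within 1 year of enrolment. Section 17.1 specifies intention-to-treat and per-protocol analyses only for data gathered after controls have been offered laser.

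**The concern.** Randomisation protects the comparison only if nobody knows the arm when entry is settled, and if everyone allocated is then counted. Neither is secured for a patient who consents remotely. If consent releases the assignment, patient and staff can know the arm when they meet for the visit at which eligibility is confirmed, and the protocol has no rule for a sinus found inflamed at that point.

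The larger exposure is loss between allocation and first treatment. A laser patient who leaves in that interval has not begun participation under section 12.1 and contributes no data. A recurrence during the wait may go unrecorded for the same reason, although section 4.1 would count it if enrolment starts the clock. Because no analysis set is stated for the 1-year outcome, these patients can disappear from one arm. If they differ in risk from those who stay, the arms differ for reasons other than treatment. Enrolling 30 more patients restores numbers, not comparability.

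**Working it through.** **1. The plan's own figures.** Section 12.1 states that "the recurrence rate within 1 year is expected to be 12% in the control group and a maximum 2% in the laser group", with two-sided 5% error and 80% power. The two-proportion formula with continuity correction gives 121 per arm against the stated 122; a small group-sequential inflation would explain the difference. Then 122 / 0.90 = 135.6, so 136 per arm; 136 + 15 = 151; 2 × 151 = 302. All reproduce, and nothing below changes them.

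**2. The order of events.**

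| Step | In person | Telehealth |
|---|---|---|
| Pre-screen by contact | before invitation | before invitation |
| Consent | initial clinic visit (13.1) | remote (13.1) |
| Criteria check in web system | before allocation (17.2) | before allocation (17.2) |
| Eligibility confirmed | initial clinic visit (10.1) | initial clinic visit (10.1) |
| Randomisation | on consent (17.2) | on consent (17.2); timing against the visit not stated |

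The Study Summary describes clinic visits by patients already randomised. Allocation before the visit is therefore permitted and plausible on the telehealth route, but it is inferred.

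**3. Size of the reported loss.** 15 / 151 = 9.9%, or 15 / 136 = 11.0% of the earlier target, reported for the laser arm only. Power is not the problem: with 136 controls and 122 laser patients analysed it is 88%, against 90% with 136 in each arm (normal approximation, no continuity correction).

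**4. Bias if those lost differ in risk (illustration).** Assume no treatment effect, a true 12% rate in both arms, 151 laser patients allocated, m removed with recurrence risk q, then 10% dropout. The remaining laser rate is (151 × 0.12 − m × q) / (151 − m). For m = 15 and q = 0.36 this is (18.12 − 5.40) / 136 = 9.35%. The chi-squared test then rejects with these probabilities (exact binomial calculation, 136 controls):

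| Removed (m) | q = 12% (average risk) | q = 36% | q = 60% |
|---|---|---|---|
| 5 | 5.0% | 5.5% | 7.1% |
| 10 | 5.1% | 7.4% | 15.1% |
| 15 | 4.9% | 10.1% | 30.4% |

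The 36% is the overall recurrence rate in the institution's chart review (section 3.1), borrowed as an assumed risk; 60% is purely illustrative. With a 20% base rate and q = 36%, the figures are 5.2%, 5.6% and 6.7%.

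**5. Cost of keeping the 15.** If they stay in the laser arm and recur at the control rate, that arm's expected rate is (136 × 0.02 + 15 × 0.12) / 151 = 4.52 / 151 = 3.0%. Power with 136 per arm analysed is 81%, still above target.

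**6. Flares during a wait (illustration).** With a constant hazard, the chance of a flare in t months is 1 − (1 − r)^(t/12). At r = 12% it is 1.1% for 1 month and 3.1% for 3 months. At the institution's 20% one-year rate it is 1.8% and 5.4%. These apply only to patients who wait that long. If an assumed 20% of 151 laser patients came by telehealth (30.2), the expected number is about 0.3 to 0.95 at the 12% rate and at most 1.6 at the 20% rate. If all 151 waited 3 months, it is under 5 at the 12% rate.

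**The case against.** The strongest reply is that the protocol never says telehealth patients are randomised before the visit. Section 17.2 has the web system verify the criteria first, and 10.1 and 13.1 screen against both criteria lists before inviting anyone. Section 13.2 treats telehealth as a way of attending the surgery clinic, so the video encounter might itself be the initial visit, and the protocol sets no method for judging active inflammation. This stands in part: loss of concealment is possible, not demonstrated. But neither check is described as including an examination, 10.1 still puts confirmation at the clinic visit, and a check at allocation cannot cover a flare that comes afterwards.

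A reader might infer from section 12.1 that the 15 departures show the telehealth route failing, or patients leaving because of the arm drawn. The documents do not support that. They attribute the departures to COVID-19 concerns and do not say how these patients consented. The halt began on March 16, 2020, and the revision adding electronic consent is dated 6/9/2020, so in-person recruits could equally have waited. What the departures do show is that the arm was known before first treatment and that loss in one arm followed with no data collected.

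A reader might also infer that inflamed laser patients are dropped while inflamed controls are counted. No passage provides for dropping a randomised patient as ineligible, and controls have an initial visit too. The gap is that such exclusion is not ruled out.

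Nor should the flare percentages be set beside the 2% laser rate. They describe a subgroup of unknown size during a one-off delay, whereas 2% is a whole-arm rate.

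**Conclusion.** The concern holds in a limited form. As written, the plan lets a remotely consented patient be allocated, and know the arm, before the visit that confirms eligibility. It also has no analysis set or common starting point that keeps patients lost after allocation in the 1-year comparison. The second gap has already had consequences: about 15 laser patients, 9.9% of 151, left without data.

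The resulting bias cannot be measured from the documents. It is negligible if those lost had average risk. It roughly doubles the false-positive rate, to 10.1%, if all 15 had a 36% risk, and is larger at higher risks. Those results rest on the assumed number removed and their assumed risk. Flares during the wait are probably a minor contributor. The change should be made, with medium confidence, because the order of events is inferred and the telehealth share is unknown.

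**What to change.** - **Sections 13.1 and 17.2:** state that telehealth consent only registers the patient, and that the web system releases the assignment at the in-person initial visit, after eligibility (including absence of active inflammation) has been confirmed. Release should be as close to the start of treatment as scheduling allows; same-day release at the first laser session is optional.
- **Section 17.2:** state that no patient is excluded for ineligibility once the assignment is released. This concerns the analysis only; clinical management is a separate matter.
- **Section 17.1:** analyse all randomised patients as allocated for the 1-year outcome, counting time from randomisation in both arms, and reconcile this with the start of participation in 12.1 and the enrolment-based window in 4.1. This also covers the roughly 15 patients already lost, whose outcomes should be sought or treated explicitly as missing.

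The cost is a change to the release step in the web system and a few sentences. Sample size is unaffected. Some telehealth patients will not attend without knowing their arm, and clinic scheduling becomes slightly less efficient, but those losses fall before randomisation and do not bias the comparison.

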#### 10.2 Inclusion Criteria

- All Fitzpatrick skin types
- Age: 11-21 years
- Previous diagnosis or concern for active pilonidal disease

#### Exclusion Criteria

- History of photosensitivity
- Actively inflamed pilonidal sinus. These patients will be informed of the trial and invited to contact the study team upon resolution of their inflamed sinus if they are interested in being in the trial at that time.

10.3 Our study will include children and teenagers. It will exclude adults unable to consent, pregnant women, and prisoners.

### 11.0 Vulnerable Populations\*

11.1 The study will be conducted within a pediatric surgery clinic and will therefore involve minors. As a pediatric research hospital we will continue to utilize the stringent privacy safeguards that are in place for all patients treated at this institution. This study falls under Section 2 or HRP 416 as it is greater than minimal risk to the participants.

### 12.0 Local Number of Subjects

12.1 The sample size needed to assess the primary outcome of the proportion of patients with recurrent pilonidal disease at 1-year is based on: 1) previous published studies and institutional data on the recurrence rates of pilonidal disease and 2) the efficacy of laser hair depilation treatment to reduce pilonidal disease recurrence in previous studies and our institutional pilot study. In this RCT, the recurrence rate within 1 year is expected to be 12% in the control group and a maximum 2% in the laser group. Based on these estimated recurrence rates, under a group sequential design with one interim and one final analysis, an overall type I error rate (two- sided) of 5 % and power of 80%, the sample size required for this trial is 122 patients in each treatment group. Assuming a 10% drop out rate over the course of the 1 year follow-up, we will plan to enroll 136 patients in each group (total; n=272 patients).

The gap in the laser treatments caused by COVID-19 created a gap in when we could begin laser treatments in newly enrolled patients by 1-3 months. Since a laser patient's participation in the study begins at their first laser treatment, no data has been collected on these patients. Patients in the group have reported no longer being interested/able to receive

treatments due to concerns about COVID and visits to the hospital to receive laser treatments. This group of about 15 patients was not anticipated for our sample size calculation but are needed for the primary outcomes data. In order to maintain the required power in our analyses, our statistician recommends enrolling and randomizing an additional 30 patients, thereby increasing our sample size to 302 patients (151 in each group).

12.2 If applicable, distinguish between the number of subjects who are expected to be enrolled and screened, and the number of subjects needed to complete the research procedures (i.e., numbers of subjects excluding screen failures.) -N/A

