598 **12 months post 1st treatment (±30 days)**

599 A member of the research team from NCH will call or email the family  
600 and ask questions about any problems the child has had with their  
601 pilonidal disease since their 9-month follow-up. Specifically, we will ask  
602 about subsequent ED/Urgent Care visits or physician visits, readmissions

603 and operations, additional imaging, and missed days from normal  
604 activities by the patient and legal guardian that were related to their  
605 pilonidal disease. We will also ask about the out-of-pocket expenditures  
606 directly spent on post-treatment medical care and returning visits (e.g.  
607 insurance copayments; costs of drugs) and other expenditures related to  
608 the visits (e.g. transportation costs) within one year. Please see the form in  
609 the appendix for data points to be collected during this phone call. For  
610 patients that are unresponsive to follow up, we will contact their primary  
611 care physician (PCP) to assess event related to their pilonidal disease.

612 For subjects who will turn 18 before their 12-month follow-up, they will  
613 be asked to sign the informed consent used for the study and to update  
614 their contact information. After speaking with the subject and explaining  
615 the study, an informed consent and contact information sheet will be  
616 mailed to the subjects to sign so that we may continue to collect data up to  
617 24 months after their initial study treatment.

618 A \$50 research debit card card will be mailed to the legal guardian's  
619 address for the completion of this time point.

620 \*If at the 12 month time point, laser depilation is shown to be effective,  
621 patients randomized to the control group will be offered laser treatment at  
622 no cost. Patients choosing to receive laser treatments at no cost will be  
623 also asked to re-consent at this time and will be asked to complete surveys  
624 at the 1, 2, 3, 4, 6, 9, and 12 months follow-up time points. However, only  
625 patients will only receive \$20 for the completion of the 6 and 9month  
626 survey completions, and a \$50 for completion of the surveys at 12 months.  
627 As we are asking this group of standard care to laser care patients to  
628 continue to fill out surveys and attend laser visits (in the same fashion as  
629 the group originally randomized to laser) we will ask these patients to  

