## **17.0 Data Management\* and Confidentiality**

17.1 The means/medians and standard deviations/interquartile ranges of the prognostic variables will be evaluated in the total study sample and will be compared between groups using t-tests or Mann Whitney U tests for continuous variables and chi-squared tests for categorical variables. For the primary outcome of recurrence within one year, we will calculate this proportion and its 95% confidence interval, based on the exact binomial distribution, in both treatment groups and compare this proportion between groups using a Chi-squared test.

Other outcomes will be compared using chi square tests, if categorical, and t-tests or Mann Whitney U tests as appropriate if continuous. In analyses that include outcome data collected after patients in the control group were offered laser treatment, both intention-to-treat and per-protocol analyses (with control group patients analyzed according to the treatment they received and according to the time from the start of their laser treatment) will be performed. SAS Enterprise Guide (Cary, NC) will be used for the statistical analyses.

The sample size needed to assess the primary outcome of the proportion of patients with recurrent pilonidal disease at 1-year is based on: 1) previous published studies and institutional data on the recurrence rates of pilonidal disease and 2) the efficacy of laser hair depilation treatment to reduce pilonidal disease recurrence in previous studies and our institutional pilot study. In this RCT, the recurrence rate within 1 year is expected to be 12% in the control group and a maximum 2% in the laser group. Based on these estimated recurrence rates, under a group sequential design with one interim and one final analysis, an overall type I error rate (two- sided) of 5 % and power of 80%, the sample size required for this trial is 122 patients in each treatment group. Assuming a 10% drop out rate over the course of the 1 year follow-up, we will plan to enroll 136 patients in each group (total; n=272 patients). The total of patients increased to 302 due to reasons related to COVID described above.

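### About 15 laser-assigned patients who never started treatment have no outcome data and no analysis rule, and the 1-year endpoint has conflicting time origins

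*Combined protocol and SAP*

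**What the plan says.** - **Endpoint (4.1).** The primary outcome counts a recurrence needing antibiotics, "additional surgical incision and drainage, or excision within 1 year of enrollment".
- **Randomisation (17.2).** Patients are randomised once they consent to enrol, so before any laser session.
- **COVID gap (Study Summary; 12.1).** First laser sessions in newly enrolled patients slipped by 1-3 months. The rule given is: "Since a laser patient's participation in the study begins at their first laser treatment, no data has been collected on these patients". About 15 of them are described as unanticipated in the sample size but required for the primary outcome. The response is 30 further randomisations, giving 302 (151 per arm).
- **Follow-up clock.** The Study Summary counts laser follow-up from the initial treatment. The 12-month contact in 6.4 is headed "12 months post 1st treatment". The general follow-up paragraph in 6.4 counts from the initial visit.
- **Analysis (17.1).** The 1-year proportions are compared by chi-squared test, with no named analysis population and no rule for missing outcomes. Intention-to-treat appears once: "In analyses that include outcome data collected after patients in the control group were offered laser treatment, both intention-to-treat and per-protocol analyses".
- **Recovery routes.** Section 6.4 says that, at 12 months, for "patients that are unresponsive to follow up, we will contact their primary" care physician. Sections 6.3 and 6.4 provide for family report and outside records, and 19.3 names the hospital record as a data source. None of these is tied to the 15.

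**The concern.** Randomisation protects the comparison only if patients are counted from the point of allocation, in the arm they were given. Here, being counted in the laser arm depends on an event after allocation: attending a first session. A patient who is assigned to laser and never attends generates no record under the Section 12.1 rule. The corresponding rule for controls is not conditional on receiving a later treatment.

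The clock raises a related problem. If a laser patient's year starts at first treatment, a recurrence after enrolment but before that session falls outside the window, although Section 4.1 would count it. The passages cannot all hold for a patient treated 1-3 months after enrolling. What is at stake is whether the primary result compares the arms as randomised or compares laser starters with all controls.

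**Working it through.** **1. The plan's own sample size.** Inputs from 12.1: "the recurrence rate within 1 year is expected to be 12% in the control group and a maximum 2% in the laser group"; two-sided 5% type I error, 80% power; "the sample size required for this trial is 122 patients in each treatment group".

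- Pooled-variance formula, mean rate 0.07: n = [1.960·√(2·0.07·0.93) + 0.842·√(0.12·0.88 + 0.02·0.98)]² / 0.10² = 101.0, so 102 per arm.
- With continuity correction: (101.0/4)·[1 + √(1 + 4/(101.0·0.10))]² = 120.2, so 121 per arm. This matches 122 closely. The uncorrected figure does not. An O'Brien-Fleming look at about 19% information spends roughly 0.000007 of alpha and adds almost nothing.
- Dropout: 122/0.9 = 135.6, so 136 per arm and 272 in total. 272 + 30 = 302, or 151 per arm.

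The stated figures reproduce.

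**2. What the increase restores.** (151 − 15) × 0.9 = 122.4 laser patients. That is the evaluable number required, so the increase restores the count. It does nothing for the outcomes of the 15, who are 15/151 = 9.9% of the arm.

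**3. As-randomised laser risk.** Assumption: the 136 treated recur at 2% and the 15 untreated at a rate r.

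Risk = (136 × 0.02 + 15 × r)/151

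- r = 12%: (2.72 + 1.80)/151 = 2.99%, and the planned difference falls from 10.0 to 9.0 points.
- r = 20%: (2.72 + 3.00)/151 = 3.79%.

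**4. Power with everyone kept.** 151 less 10% gives 136 evaluable per arm, with control risk 12%. Power by exact enumeration of the chi-squared test:

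| r in the 15 | Laser risk | Uncorrected | Continuity-corrected |
|---|---|---|---|
| 2% | 2.0% | 93% | 89% |
| 5% | 2.3% | 91% | 86% |
| 12% | 3.0% | 84% | 77% |
| 20% | 3.8% | 73% | 65% |

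The usual approximate formula gives lower values at r = 12%: 81% and 74%. By that formula, 80% power needs 134 evaluable per arm (149 enrolled) uncorrected, or 155 (173 enrolled) corrected.

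**5. Sensitivity of the test result.** Take results near the planned rates: 16/136 control against 2/122 laser, uncorrected p = 0.0014. Adding the 15 gives 137 laser patients. Five recurrences among the 15 (7/137) give p = 0.048, and six (8/137) give p = 0.084.

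**6. The clock.** Assumption: constant hazard, 12% a year before laser and 2% a year from the first session.

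- Risk in the uncounted window: 1 − 0.88^(1/12) = 1.1% for one month, 1 − 0.88^(3/12) = 3.1% for three.
- Both clocks cover 12 months, so the late one swaps an early window for a later one. From enrolment, the 12-month risk is 1 − 0.88^(1/12)·0.98^(11/12) = 2.9%, or 1 − 0.88^(3/12)·0.98^(9/12) = 4.6%. Against 2.0% from first treatment, the net change is 0.9 to 2.6 points per delayed patient.

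The documents do not say how many patients started late.

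**The case against.** The strongest reply is that the plan nowhere says the 15 will be excluded or replaced. It calls their outcomes necessary, Section 17.1 compares both treatment groups without restricting to treated patients, and Section 4.1 still counts from enrolment. That they were randomised is itself inferred, from the label laser patient and from Section 17.2. Recovery routes exist, and Section 14.2 lets a patient switch to standard treatment without leaving the study. All of this is fair. Omission is the likely consequence of having no data, no recovery plan and no analysis set; it is not a stated decision.

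A reader might go further than the documents allow in four ways:

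- *That the omission favours laser.* The stated reasons for not starting are COVID and hospital visits, not disease course. If laser had no effect and the 15 were unselected, dropping them would not inflate error: at 12% in both arms with 136 against 122 patients, exact type I error is 4.9% uncorrected. If laser works and the 15 recur like controls, the 10- and 9-point differences describe laser when received and laser as assigned. Distortion under no effect requires prognostic selection, which is possible but not shown.
- *That no control was lost in a similar way.* Research appointments were halted generally, controls also have an initial clinic visit, and no control count is given.
- *That about half the laser events vanish.* This comes from giving the 15 the 20% institutional 1-year rate (3.1) while the plan holds controls at 12%: 3.00 of 5.72 expected events. It mixes two risk levels. The 20% row in the power table is likewise only a stress case in which the 15 have a worse prognosis than planned controls.
- *That the late clock is a further loss on top.* It exchanges windows, and the only delayed group with a number is the same 15 or so.

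**Conclusion.** The concern stands as a defect in the plan as written, beyond missing detail. Section 12.1 states an operating rule under which about 10% of the planned laser arm has no outcome data, and the added recruitment repairs only the count. The endpoint and follow-up clocks contradict each other, and the primary 1-year test has no defined population. It should be corrected before the primary analysis.

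The direction and size of any bias cannot be stated, because the outcomes were not collected. The shift from 2.0% to about 3.0% in laser risk is an illustration that rests on a 12% rate in the 15. On planned results it would take about six recurrences among the 15 to lose uncorrected significance, so the main exposure is the effect estimate. The sample-size arithmetic is correct for its own assumptions, but 302 does not clearly give 80% power once the 15 are kept: under the continuity correction that reproduces 122, power is about 77% if they recur at 12%. These figures also assume 10% loss in each arm.

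**What to change.** 1. **Time origin.** In 4.1, 6.4, 12.1 and 17.1, use one origin, randomisation or enrolment, for both arms. State that recurrences before the first laser session count.
2. **Analysis set.** In 17.1, make the primary chi-squared analysis all randomised patients in their assigned arm. A change to time-to-event methods is not needed for this.
3. **Outcomes of the 15.** In 12.1, say that their 12-month outcome will be sought by survey, record review and primary care contact, unless consent was withdrawn.
4. **Sensitivity analyses.** Prespecify one for missing outcomes, with a treated-only analysis as a further one.
5. **Sample size.** Restate the power for 302 on the as-randomised basis, saying whether the test is continuity-corrected and giving a range for recurrence in the 15.

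The cost is protocol wording and about 15 outcome checks. The expected effect becomes slightly smaller (about 9 points rather than 10 at the 12% assumption), and the stated power is lower than it would be with the 15 left out.
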